## Abstract

**Background:**

Mental health has come to be understood as not merely the absence of mental illness but also the presence of mental well-being, and recent interventions have sought to increase well-being in various populations. A population that deserves particular attention is that of health care workers, whose occupations entail high levels of stress, especially given the ongoing COVID-19 pandemic. A neuroscience-based web-based well-being program for health care workers—the Thrive program—has been newly developed to promote habits and activities that contribute to brain health and overall mental well-being.

**Objective:**

This paper describes the protocol for a randomized controlled trial whose objective is to evaluate the Thrive program in comparison with an active control condition to measure whether the program is effective at increasing well-being and decreasing symptoms of psychological distress in health care workers at a designated Australian hospital.

**Methods:**

The trial will comprise two groups (intervention vs active control) and 4 measurement occasions over a 12-week period. A survey will be administered in each of weeks 0, 4, 8, and 12, and the well-being program will be delivered in weeks 1-7 (via web-based video presentations or digital pamphlets). Each of the 4 surveys will comprise a range of questionnaires to measure well-being, psychological distress, and other key variables. The planned analyses will estimate group-by-time interaction effects to test the hypothesis that mental health will increase over time in the intervention condition relative to the active control condition.

**Results:**

The Thrive program was delivered to a small number of wards at the hospital between February 2021 and July 2021, and it will be delivered to the remaining wards from October 2021 to December 2021. A power calculation has recommended a sample size of at least 200 participants in total. A linear mixed model will be used to estimate the interaction effects.

**Conclusions:**

This trial seeks to evaluate a new web-based well-being program for health care workers at a major public hospital. It will contribute to the growing body of research on mental well-being and ways to promote it.

**Trial Registration:**

Australian New Zealand Clinical Trials Registry ACTRN12621000027819; https://tinyurl.com/58wwjut9

**International Registered Report Identifier (IRRID):**

DERR1-10.2196/34005

## Introduction

### Background

In recent decades, the medical and behavioral sciences have recognized that mental health is not merely the absence of mental illness but also the presence of mental well-being [1]. Thus, mental illness and well-being are distinct albeit related constructs that need to be considered in research and clinical practice. In a seminal study of the US adult population, Keyes [2,3] delineated three categories of mental well-being: flourishing, moderately healthy, and languishing. Those with high well-being and no mental illness are described as flourishing, whereas those with low well-being may be free of illness (*pure languishing*) or not (eg, *depressed and languishing* in the case of those with major depression). In the representative sample of >3000 adults, less than one-fifth were flourishing, and a comparable proportion were languishing. Of those with low well-being, over half did not meet criteria for a major depressive episode, generalized anxiety disorder, panic disorder, or alcohol dependence over the preceding 12 months. On average, those who were purely languishing reported less than one symptom of each of these disorders, suggesting that low well-being is not a proxy for subclinical illness but rather a distinct condition. This was supported by confirmatory factor analyses that indicated that a correlated 2-factor model was the best way to account for the data on mental illness and well-being. Furthermore, it was found that pure languishing was not only as prevalent as pure illness (ie, illness without low well-being) but also associated with more severe psychosocial outcomes (relative to pure illness) on 9 out of 11 measures. Clearly, low mental well-being can place a substantial burden on the individual and on society that stands apart from the costs of illness alone and needs to be targeted in its own right in health promotion strategies.

More recently, there have been important advances in the measurement and understanding of mental well-being. [name] et al [4] developed a composite measure of well-being—the Composure, Own-worth, Mastery, Positivity, Achievement, and Satisfaction for Wellbeing (COMPAS-W) scale—that assesses both hedonia (ie, positive affect and life satisfaction) and eudaimonia (ie, fulfillment of one’s potential and having a sense of life purpose) across six subcomponents: Composure (dealing effectively with stress or adversity), Own-worth (a sense of autonomy and self-respect), Mastery (self-confidence and perceived control over one’s environment), Positivity (happiness and optimism), Achievement (setting and pursuing goals), and Satisfaction (with one’s life, health, and relationships). This factor structure was confirmed in a major twin study of Australian adults, as was the scale’s reliability and validity. For example, well-being was associated with lower levels of depression, anxiety, and stress symptoms; higher work productivity; and healthier diet, exercise, and sleep habits [4]. The COMPAS-W measure has allowed researchers to explore the genetic and neural underpinnings of mental well-being [5-7] and, crucially, to determine the extent to which well-being might be modifiable through interventions and other environmental influences. From their twin study, [name] et al [4] derived heritability estimates between 24% and 48% across the 6 subcomponents of well-being, with the remaining variance attributed to the unique environment. This indicates that, although well-being is significantly influenced by genetic factors, it is certainly subject to external influences as well, which is encouraging for practitioners who would seek to raise levels of well-being in a given population.

As mental well-being has been recognized as a key construct in its own right and one that is substantially determined by nongenetic factors, it has become the focus of interventions that aim to elevate it or at least prevent its decline. To date, there have been 2 randomized controlled trials (RCTs) investigating the effects of an intervention on COMPAS-W scores. In a trial involving a subsample from the aforementioned twin study, Routledge et al [8] evaluated a 30-day *brain training* (ie, computerized cognitive training) program comprising games and exercises related to cognitive and affective processing as well as emotional regulation. Relative to a waitlist control group, training participants exhibited changes in explicit emotion identification and implicit emotion bias for a number of facial expressions, but these alterations did not lead to changes in well-being or psychological distress. However, the brain training program did not exclusively target mental health but rather comprised a broader set of cognitive and emotional activities, and many participants did not complete the minimum amount of training recommended by the researchers. Furthermore, the recruitment process excluded participants with current or lifetime psychiatric disorders or substance abuse. Therefore, there may have been a ceiling effect whereby many participants were already functioning well enough that they had little to gain from the intervention in that regard, especially if they did not complete the recommended amount of training.

In the second RCT study, Chilver and [name] [9] evaluated a 6-week positive psychology intervention relative to an active control condition in 326 university students. They found that the intervention led to significant increases in subjective well-being and—in those who had low resiliency resources at the outset—increases in composite well-being and decreases in psychological distress (ie, depression and anxiety symptoms). Again, this is consistent with the possibility that a ceiling effect exists to some degree whereby those who are more mentally healthy at the outset have less to gain from an intervention. However, across all the participants, the intervention by Chilver and [name] [9] resulted in significant increases in the well-being subcomponent of Satisfaction, suggesting that certain aspects of well-being may be more responsive to training even in those with higher resilience at baseline. Together, these studies suggest that it is possible to improve well-being outcomes via particular intervention approaches and that they may be more efficacious in populations that are less resilient or more exposed to stress and other kinds of adversity.

One such population to target is hospital-based health care workers, who work under demanding and stressful conditions. There is extensive literature on nurses’ experiences in the workplace, highlighting a range of demands and hardships that can compromise staff well-being. For instance, in a survey of >40,000 nurses from >700 hospitals across 5 countries, Aiken et al [10] found that the proportion of nurses who reported job dissatisfaction was >40% in the United States; >30% in Canada, England, and Scotland; and approximately 20% in Germany. For comparison, the researchers pointed out that job dissatisfaction in the general population of American professionals was only 10%, indicating that dissatisfaction was markedly higher among nurses. Furthermore, a large proportion (15%-40% depending on the country) of the surveyed nurses reported that they were planning to leave their job in the following year. In a more recent survey of >3000 Australian health care workers, >70% stated that their workloads exceeded what they were capable of doing well at least once or twice a week, and >25% stated that they were thinking of leaving their profession [11]. The typical sources of psychological distress reported by health care workers include heavy workloads, time pressures, role ambiguity, lack of control or flexibility, and lack of participation in decision-making [12].

The COVID-19 pandemic has placed additional demands on health care workers [13]. In Australia, a survey of 637 primary health care nurses [14] revealed that most respondents (nearly 75%) did not always have access to sufficient personal protective equipment, almost half had concerns about a lack of support from their employers, and over one-third stated that the quality of care at their workplace had diminished (at least slightly) since the start of the pandemic. In addition, the government of New South Wales (Australia’s most populous state) published a summary of worldwide research on the impact of the pandemic on the mental health of health care workers [15], finding that the pandemic had placed these workers at increased risk of psychological distress, including anxiety about contracting the virus. Of 433 Australian health care workers surveyed, approximately 50% reported increased workloads, anxiety, and tiredness, and >70% reported higher stress at work.

The mental well-being of nurses and other health care workers is vitally important not only for the workers themselves but also for the health and safety of their patients. Structural equation models have suggested that well-being mediates the relationship between organizational factors and patient care. For example, a study of 324 Hong Kong nurses [16] found that nurses’ perceptions of support from their workplace, supervisor, and colleagues predicted their psychological well-being, which in turn predicted their safety performance. Similarly, a study of 345 Iranian nurses [17] found that organizational support predicted psychological well-being, which in turn predicted both job satisfaction and quality of care, and a study of 474 Taiwanese nurses [18] concluded that well-being predicted safety attitudes. In addition, a study of 325 Pakistani nurses found that those with higher levels of negative emotion were judged by their peers to engage in higher levels of “deviant” workplace behavior such as deliberately arriving late to work or taking undeserved breaks to avoid doing work, which could compromise patient care in numerous ways [19]. Furthermore, in a study of 637 US nurses, Dyrbye et al [20] observed that those who scored lower on a well-being index were more likely to have made a patient care error in the previous 3 months. Although the relationship between well-being and patient care may go in either direction (or be attributable to a third variable), it is eminently plausible that low well-being (and the psychosocial dysfunction that comes with it) can result in suboptimal job performance and more frequent errors (cf Keyes [3], who found that lower well-being was related to higher absenteeism and reduced workdays, and [name] et al [4], who found that lower well-being was associated with higher absenteeism and lower productivity on the job). Clearly, there are substantial benefits that may be gained by addressing shortfalls in health care workers’ well-being.

Fortunately, there is some research to suggest that interventions for health care workers can lead to reductions in stress and improvements in mental well-being [21], although the evidence base is relatively limited at present. For instance, Orly et al [22] administered a cognitive behavioral intervention for nurses that resulted in benefits related to stress and mood, but the sample size was small (N=36), the participants were not randomly allocated to the intervention and control conditions, and there was no follow-up (ie, no testing beyond the end of the intervention). Tveito and Eriksen [23] conducted an RCT of a health and fitness program for nursing home staff, finding benefits in terms of self-reported health and stress but, again, the sample was small (N=29), and there was no follow-up. Similarly, Daigle et al [24] conducted an RCT of a mindfulness-based stress-reduction program for nurses, finding improved mood in the intervention group but, yet again, the sample was small (N=52), and there was no follow-up. Similarly, Bolier et al [25] carried out an RCT of a web-based mental health program for health care workers, but the randomization was conducted at the ward level rather than the individual level and, of the 178 participants allocated to the intervention group, only 9 actually engaged in the web-based activities. Hence, our study seeks to address some of the gaps in the literature on well-being programs for health care workers.

This paper outlines the protocol for an RCT evaluating the effects of a new well-being program—the *Thrive* program—for health care workers at a large public hospital in metropolitan Sydney, New South Wales, Australia. Thrive is a web-based psychoeducational program that provides information and guidance within seven areas of life related to mental well-being: sleep, exercise, nutrition, stress management, social connection, cognitive challenge, and life purpose. The program is innovative in that it covers how these 7 aspects of life affect not only well-being in general but also brain health in particular. With advances in neuroscience and neuroimaging in the 21st century, there is now a sufficient knowledge base to underpin this specialized intervention, which is aimed at promoting well-being via healthy habits and lifestyle decisions that directly affect the organ on which mental health ultimately depends—the brain. Another key strength of this study is that the COMPAS-W well-being scale [4] will be used as the primary outcome measure, allowing for a comprehensive assessment of the participants’ subjective and psychological well-being and an opportunity to detect whether one or more of the 6 subcomponents of well-being is more or less responsive to the intervention. To the authors’ knowledge, this will be the first intervention for health care workers to use an empirically derived measure of well-being that has also been validated with regard to genetic [7,26-28] and neural [5,6,29] markers as well as psychological factors, including resilience, trauma, and coping strategies [30,31].

### Objectives

This study has 2 main objectives. First, it aims to determine whether the Thrive program results in significant gains in well-being—as measured by the COMPAS-W scale—in the intervention group compared with an active control group and, if so, which of the specific COMPAS-W subcomponents is most responsive to the program. Second, from the baseline measurements, the study will inform researchers, hospital staff, and other stakeholders of the current levels of overall mental health and well-being among the health care workers at the target hospital.

## Methods

### Design

The Thrive program will be evaluated in an RCT with 2 conditions and 4 measurement occasions. Thus, there will be two main independent variables—one between-group factor and one repeated-measure factor—as well as a selection of covariates and dependent variables. The two conditions will be the intervention (ie, the Thrive webinar program) and an active control condition (only an abbreviated pamphlet version of the educational components of the program). The study will take place over a 12-week period, and a web-based survey will be administered at each of the 4 measurement occasions. In week 0 (ie, 1 week before the program commences), the participants will complete the baseline survey (before the intervention). The Thrive program (and the parallel active control program) will run for 7 weeks, from week 1 to week 7. The participants will complete the second survey in week 4 (at the midpoint of the program), the third survey (after the intervention) in week 8 (ie, 1 week after the conclusion of the program), and the fourth survey (follow-up) in week 12 (ie, 4 weeks after the intervention). Each survey will take approximately 20 to 30 minutes to complete. Once all 4 surveys have been administered and the study period has concluded, all the participants in the active control condition will be given access to the full version of the Thrive program. The study timeline is illustrated in Figure 1.

**Figure 1 figure1:**
[figure not shown]
Study timeline.

### Participants

The participants will be health care workers from the Prince of Wales Hospital (POWH), a large public hospital in metropolitan Sydney, New South Wales, Australia. The participants will be recruited via flyers displayed around the hospital, emails sent to hospital staff mailing lists, and announcements from management (eg, Nursing Unit Managers). All health care workers from the hospital (eg, nurses, physicians, and allied health professionals) will be welcome to sign up for the study.

### Eligibility Criteria

Prospective participants will be eligible to enroll in the study provided that they are health care workers at POWH, comfortable using written English to complete the program and surveys, willing to take four 20-to-30–minute web-based surveys across the 12-week study period, willing to complete the 7-week well-being program, and able to access the internet for the surveys and program content.

### Recruitment

Study advertisements will invite POWH staff to sign up for the 12-week study and notify them that participants will be randomly assigned to one of two conditions, labeled *online presentations* and *take-home readings*. Those assigned to the former condition will be the intervention group, and those assigned to the latter condition will be the active control group. Once assigned, the participants will know whether they are in the *online presentations* or *take-home readings* condition, but they will be blind to which condition is the true intervention versus the active control. They will also be assured that all participants in one version of the Thrive program will receive all the resources of the other version after the end of the 12-week study period. This assurance should reduce the incentive for participants in one group to share any course content with a participant from the other group (the participants will also be explicitly instructed not to share anything with anyone else throughout the program).

Potential participants will be informed that those who complete the Thrive program will be eligible to receive Continuing Professional Development (CPD) points. At POWH, nurses and other health care workers are expected to engage in ongoing professional development by attending workshops, completing courses, and participating in other such activities, with a certain number of CPD points awarded for each activity. Each worker has to earn at least 20 points per year, and each Thrive participant will receive 10 points after completing the program. As the control participants will gain access to the full Thrive program at the end of the 12-week study period, all the participants will receive 10 points regardless of the condition to which they are assigned. There are numerous ways outside the Thrive program in which a given health care worker can earn their required CPD points, so the offer of 10 points for completing the program is not an undue inducement to participate but rather fair compensation for the participants’ time and effort. Each participant will also receive a Certificate of Completion from the research team.

### Randomization and Informed Consent

Hospital staff interested in participating will sign up for the study by writing their details (ie, name, email address, and ward) on registration sheets posted around the wards, by registering on the web via the hospital’s professional development website, or by emailing a designated member of the research team (MM). The final list of participants will be sorted according to ward to allow for stratified randomization. For each ward, a random number generator will be used to allocate half the participating staff to the intervention condition and half to the active control condition. Next, the participants will be notified by email as to the condition to which they have been assigned. This email will also provide the Participant Information Statement and Consent Form and a link to the first survey. After reading the form, those who are willing to participate will click on the link to access the first survey. The first item of this survey provides a button whereby the participant can digitally record their consent to participate. For the remainder of the study period, the participants will be sent the relevant survey links and program resources by email at the appropriate times.

All participants will be free to withdraw at any time from the surveys, the Thrive program, or both the surveys and the program without penalty and without having to give a reason, with the provision that only those who complete the Thrive program will receive the 10 CPD points and Certificate of Completion. However, completion of the surveys will not be required to earn the points and certificate. In other words, if a participant is enjoying the program and wishes to finish it but does not want to continue providing data via the surveys, they will be welcome to do so.

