### Primary and Secondary Outcomes

The primary outcomes for this RCT will be the participants’ levels of well-being (as measured by the COMPAS-W) and their levels of psychological distress (as measured by the Depression, Anxiety, and Stress Scale–21-item version). Thus, the primary outcomes will encompass both dimensions of mental health: mental well-being and mental illness. The secondary outcomes will be health and lifestyle habits, mood states, compassion (for oneself and others), mindfulness, work performance, and work engagement. Program attendance, resiliency resources, medical history, trauma, coping styles, and pandemic-related variables will serve as potential moderator variables along with demographic variables such as age, sex, ward, and occupation. The primary end point for the analysis will be the third measurement occasion (week 8), and the secondary end points will be the second and fourth occasions (week 4 and week 12).

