### Analysis

Missing values in the data set will be estimated via multiple imputation, and the initial analyses will be conducted on an intention-to-treat basis followed by per-protocol analyses to account for levels of treatment compliance (eg, program attendance). The data will be analyzed via a linear mixed model that will allow the group-by-time interaction effects to be estimated. It is hypothesized that levels of well-being will increase over time in the intervention condition relative to the active control condition. Similarly, it is hypothesized that levels of psychological distress (ie, symptoms of depression, anxiety, and stress) will decrease over time in the intervention condition relative to the active control condition. There may also be a group-by-time interaction effect on one or more of the secondary outcomes. For example, the intervention may promote increased compassion, mindfulness, or work engagement. Furthermore, any interaction effect may itself be moderated by a variable such as resilience or coping style (cf [9,31]).

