## Results

The trial has been prospectively registered with the Australian New Zealand Clinical Trials Registry (registration approved on January 14, 2021; trial ID ACTRN12621000027819).

The Thrive program was developed between August 2020 and January 2021. For logistical reasons, it was decided that the program would be implemented incrementally throughout the hospital. The hospital comprises >50 wards, of which 5 were selected for the initial wave of recruitment, which occurred in December 2020 and January 2021. For the resulting cohort of participants, survey 1 was administered in February 2021, survey 2 was administered in March 2021, survey 3 was administered in April 2021, and survey 4 was administered in May 2021. The participants in the active control condition were provided with the full version of the program between May 2021 and July 2021. CPD points and certificates were awarded in August 2021. Since the successful administration of the Thrive program in the initial selection of wards, the research team and hospital management have decided to continue rolling out the program, and the staff from the remaining wards will be invited to participate in the trial from October 2021 to December 2021.

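### Allocation is stratified by ward and recruitment runs in two waves, but the described model names neither; a modest, nearly free gain in precision, and ward is a poor moderator

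*Protocol article*

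**What the plan says.** - **Allocation** (Protocol article, Randomization and Informed Consent): "The final list of participants will be sorted according to ward to allow for stratified randomization", and "For each ward, a random number generator will be used to allocate half the participating staff to the intervention condition", with the other half going to the active control.
- **Waves** (Results): "The hospital comprises >50 wards, of which 5 were selected for the initial wave of recruitment". For that cohort "survey 1 was administered in February 2021", and its fourth survey was in May 2021. After that, "the staff from the remaining wards will be invited to participate in the trial from October 2021 to December 2021".
- **Model** (Analysis): "The data will be analyzed via a linear mixed model that will allow the group-by-time interaction effects to be estimated". Neither ward nor wave is mentioned there. The Design section says there will be covariates but does not list them.
- **Missing data and population** (Analysis): "Missing values in the data set will be estimated via multiple imputation, and the initial analyses will be conducted on an intention-to-treat basis".
- **Role of ward** (Primary and Secondary Outcomes): ward is one of the possible moderators, "along with demographic variables such as age, sex, ward, and occupation". No other analytic use of it is stated.

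**The concern.** A factor used to stratify randomisation would normally be carried into the primary analysis, so that the standard error reflects the balance the design achieved. Here the article gives ward a different job, effect modification, which a trial of this size supports poorly. The decision to recruit in two waves is reported in the Results section, and the description of the analysis does not take it up. The waves start about eight months apart, in a pandemic that the article itself treats as affecting staff mental health. A single common time course may therefore fit neither wave well. At stake are the width of the confidence interval for the week-8 effect and whether any ward moderator result could be read.

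**Working it through.** **Plan's own figures (Sample Size).** Inputs: partial η² 0.01, α 0.05, correlation 0.5, 2 groups, 4 occasions. f² = 0.01/0.99 = 0.0101; λ = N × 4 × f²/(1 − 0.5); df = 3 and 3(N − 2). Power is 0.799 at N = 136 and 0.806 at N = 138, so 69 per group reproduces. 69/0.7 = 98.6, so 99 per group, 198 in total, rounded to 200. Completers at 200 recruited: 200 × 0.7 = 140.

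**Participants per ward.** This assumes every ward joins and recruitment stops at 200.
- Recruited: 200/50 = 4.0; 200/51 = 3.9.
- Completers: 140/50 = 2.8; 140/51 = 2.7; per arm 2.8/2 = 1.4.
- The average falls below 3 once 140/3 = 46.7 is passed, so from 47 wards upward.
- SE of a ward-specific arm difference: √(2/2) = 1.0 SD with two per arm, and √(2/1.4) = 1.2 SD with 1.4 per arm. The 95% half-width is then 1.96 × 1.0 = 2.0 SD to 1.96 × 1.2 = 2.4 SD.
- Chance that a ward with two per arm keeps at least one completer in each arm at 30% dropout: (1 − 0.3²)² = 0.83.

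**Stable ward differences.** Assumed layout: 50 wards × 4 people, 2:2 within ward, outcome SD 1, correlation 0.5. Variance of a change score = 2(1 − 0.5) = 1. Variance of the week-8 group-by-time term = 1 × (1/100 + 1/100) = 0.0200, so SE = 0.1414. A constant ward level drops out of every change score, so the SE is 0.1414 with or without a ward intercept at assumed ward ICCs of 0.02, 0.05 and 0.10. With 30% monotone dropout the generalised least squares SEs without and with the intercept differ by less than 0.1% (largest gap 0.1552 against 0.1551).

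**Ward-by-time differences.** Suppose a share τ of outcome variance is ward-specific at each visit. A change score then carries 2τ that is common to the ward, and this cancels between arms within the ward. The true variance is 0.0200 × (1 − 2τ), while a model without the term reports 0.0200.
- τ = 0.03: 0.0188; ratio 1/0.94 = 1.064.
- τ = 0.06: 0.0176; ratio 1/0.88 = 1.136.

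These are complete-data values; dropout makes them somewhat smaller.

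**Wave-by-time differences.** Let p be the share of participants in one wave and d the difference between waves in mean change. Omitting wave-by-time adds p(1 − p)d² to a change-score variance of 1.
- d = 0.2, p = 0.10: 0.09 × 0.04 = 0.0036 (0.4%).
- d = 0.5, p = 0.10: 0.09 × 0.25 = 0.0225 (2%).
- d = 0.5, p = 0.50: 0.25 × 0.25 = 0.0625 (6%).

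**Validity and choice of ward term.** In a simulation of change scores in the same layout (30% dropout, 2,000 runs per setting), type I error without ward was 4.3% to 5.6%. With about 50 fixed ward terms the mean SE rose from 0.169 to between 0.173 and 0.182. Power at an assumed 0.45 SD fell from about 76% to between 68% and 73%.

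**The case against.** The strongest reply is that the article only sketches the model. It gives no list of fixed and random terms, it mentions covariates, and the detail is commonly left to an analysis plan that is not shown. A reader might infer that the planned model excludes ward and wave. The documents do not support that; they show only that the description names neither. This part of the reply stands.

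It also stands that the planned test is a within-person contrast. A reader might apply the usual factor 1/(1 − ICC), giving 2%, 5% and 11% at ICCs of 0.02, 0.05 and 0.10. Those figures belong to a raw arm difference at a single visit and not to group-by-time, where the gain from a ward intercept is nil or nearly so.

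Third, the moderator list is exploratory and commits to no ward analysis. A reader might say that ward effects cannot be estimated at all. That goes too far: most wards would keep both arms, and a ward-by-treatment variance could be fitted. The count below three is an average that depends on nearly all wards joining. The target is at least 200, and under intention to treat with imputation the relevant average is about 4.

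The reply does not dispose of everything. The article does assign ward a role, and it is the one the numbers support least. Nothing in it reflects the split into two waves.

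**Conclusion.** The point holds as a modest, nearly free improvement. Treatment is balanced within each ward, and each ward belongs to one wave, so neither factor can confound the comparison, and the simulation shows no inflation of type I error. The possible cost is a reported variance that is too large: about 0.4% to 6% for wave and about 6% to 14% for ward-by-time. Both ranges rest on assumptions: a trend difference of 0.2 to 0.5 SD with 10% to 50% of participants in one wave, and a ward-by-time share of 3% to 6%. The article gives no ward ICC, no wave sizes and no number of participating wards. If time courses are alike across wards and waves, nothing is lost. Ward as a moderator would give estimates with an SE of about 1.0 to 1.2 SD each, which could be computed but not usefully interpreted.

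**What to change.** - Add fixed wave and wave-by-time terms to the primary mixed model, and carry them into the imputation model.
- Include ward as a random effect that can vary by time. An intercept alone gains essentially nothing, and about 50 fixed ward terms cost power.
- Drop ward as a moderator, or replace it with a few ward types specified in advance.
- State this before second-wave outcomes are examined, so that the adjustment is not chosen after the fact.

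The cost is a few extra model terms. Ward is already listed as an analysis variable. Because responses are anonymous and the survey platform stores no metadata (Anonymity and Confidentiality), wave should be recorded as an explicit field when each cohort's data are downloaded.
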